**Figure 2 figure2:**
[figure not shown]
CONSORT flow diagram of the OnTrack Diabetes main randomized controlled trial.

### Recruitment and Sample

Recruitment strategies for the trial are primarily community-based: newspaper advertisements, health organization newsletters, radio broadcasts, notice board postings, bulletins, emails, and online advertisements. Targeted methods include the distribution of study flyers and posters to medical centers, letters to health institutions, pharmacies and health professionals, and featuring the OnTrack Diabetes website URL on statewide Diabetes Australia research Web pages. Attendance at diabetes-related expos and events allows in-person recruitment and further promotion of the project to health professionals.

The trial aims to enroll at least 210 participants. Selection criteria include (1) type 2 diabetes diagnosis (by a medical doctor and according to World Health Organization criteria) of at least 3 months duration, (2) age 18 years or older, (3) living in Australia without plans to leave within 12 months, (4) regular computer and Internet access, (5) contactable by phone, (6) clear command of written English (at least Year 5 education), and (7) stable diabetes pharmacotherapy (medication dose stable ≥4 weeks; medication type stable ≥3 months). Study exclusion criteria include (1) current diagnosis of mental disorder other than depression or anxiety (participant is asked if a condition has been diagnosed and if so they are informed that they will receive access to the program but not be included in the trial), (2) current suicidal risk (assessed via suicide risk assessment), (3) significant cognitive disorder (eg, from head trauma or dementia), (4) currently on steroid medication or likely to commence it in the next 12 months, and (5) pregnant or likely to become pregnant in the next 12 months.

All participants are asked to undertake a medical assessment by their general practitioner prior to study enrollment. Individuals with physical limitations or concurrent physical disorders are advised of the need to exercise caution in setting physical activity goals according with their doctor’s advice.

### Measures

Primary outcomes include diabetes self-care behaviors, HbA_1c_ level, and diabetes-specific distress. Secondary outcomes include depression, anxiety, (medication taking, nutrition intake, physical activity, and blood glucose self-monitoring), quality of life, and user evaluations of the program. Measures are administered at baseline and the 3-, 6-, and 12-month follow-up time points. Table 1 in Multimedia Appendix 1 lists the measures.

### Procedure

Participants register interest on the study website and select a time to undertake an eligibility screening appointment by phone. Eligible individuals undertake baseline measures by email and phone interview at their selected appointment time. Individuals who satisfy all criteria except inclusion criterion time since diagnosis or stable medication are asked if they wish to be recontacted for future screening; if so, they are categorized as “pending.” Individuals who are ineligible are allowed to use the program without being enrolled in the trial.

Following baseline measures, all participants who are randomly allocated to the immediate access or the immediate access plus FIT interventions receive a secure username and password with which to log on to the program. Those enrolled in the delayed access condition are informed that they will receive program access details in 3 months. Computer-generated randomization occurs automatically. One week before the due date for follow-up study measures, participants receive an email notification with a link to the online survey and a preset time for the timeline follow-back procedure phone interview. The email requests that participants email the researcher if the phone interview time does not suit them.

### Delayed Access

In this condition, participants undertake their usual diabetes care with no Web-based program access. Following 3-month follow-up study measures, they receive access to the full OnTrack Diabetes program. Their access to the program is actioned by a member of the research team after which they receive an email that contains an exclusive username and password to access the program.

### Immediate Access

Participants receive access to the full OnTrack Diabetes program from baseline as described in the companion paper about the development of OnTrack Diabetes [62]. This includes access to extensive information resources, a nutrition module (Eating Well and Feeling Healthy), a module focused on adherence to health regimens (Health Routines), an emotional well-being module (Thinking Well and Feeling Fine), and a maintenance module (Keeping On Track). The first section of each module includes a series of interactive tools that incorporate guided imagery, planning goal implementation, goal setting, and confidence building. The planning tools guide participants in proceeding toward their own personalized goals in incremental steps. The second section of each module is entitled “More on...” (eg, More on Health Routines) and involves setting a weekly schedule to increase participation in desired health behaviors and pleasurable activities, and tools for problem-solving challenges. A printable summary is provided on completion of each interactive tool. These summaries can be accessed on future occasions and participants can also complete tools or modules repeatedly if they wish. Self-monitoring tools allow daily monitoring of highest and lowest blood glucose levels, best and worst mood, and the degree that physical activity and nutrition goals were met. Automated feedback graphs on progress are provided for the past week, month, or 3 months. Mindfulness audios are playable on the computer or can be downloaded to an MP3 player.

### Immediate Access Plus Functional Imagery Training

In addition to content received in the immediate access condition, participants in this condition receive regular therapist support phone calls wherein FIT techniques are utilized. The therapist is a provisionally registered psychologist who contacts participants twice in the first week of study enrollment and once in the second and third week of enrollment followed by biweekly calls. Calls last for an average of 30 to 40 minutes until the participant has been enrolled for 1 month, after which they last approximately 20 minutes. Participants are encouraged to practice FIT at home every day. The approach assists them to develop and maintain personalized changes to their diabetes self-care behaviors, alcohol use, smoking, or lifestyle. The therapist reinforces the imagery-based activities already included in the OnTrack Diabetes program and extends these by encouraging additional imagery rehearsal to further enhance motivation.

### Statistical Analyses

Preliminary analyses assess for baseline differences and subsequent analyses control for any observed differences. The primary analyses will comprise multiple regressions, predicting posttreatment and follow-up results from baseline measures and treatment contrasts with multiple imputation being used to predict missing data. Mixed-model ANOVAs with repeated measures will also be applied to confirm whether effects are still obtained without imputations. Both methods allow an intention-to-treat approach to the data. Repeated measures ANOVAs will be used to evaluate differences in change scores between the study time points among the 3 study conditions.

User satisfaction, perceived ease of use, and usefulness are examined with ANOVAs and program reach, acceptability, implementation feasibility, and outreach are assessed using the Reach Effectiveness Adoption Implementation Maintenance (RE-AIM) framework [64]. This will be operationalized using the OnTrack Diabetes Evaluation Questionnaire, which asks about users’ perceptions of the program’s acceptability, issues with feasibility, and outreach (ie, ability to access the program and barriers to access including poor broadband network availability). The inclusion of residents of rural and regional areas enriches this evaluation as will quantitative data about participants’ exposure to the program.

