**Methods:**

A small pilot trial is conducted that primarily tests program functionality, efficacy, and user acceptability and satisfaction. This is followed by the main RCT, which compares 3 treatments: (1) delayed program access: usual diabetes care for 3 months postbaseline followed by access to the full OnTrack Diabetes program; (2) immediate program: full access to the self-guided program from baseline onward; and (3) immediate program plus therapist support via Functional Imagery Training (FIT). Measures are administered at baseline and at 3, 6, and 12 months postbaseline. Primary outcomes are diabetes self-care behaviors (physical activity participation, diet, medication adherence, and blood glucose monitoring), glycated hemoglobin A1c (HbA1c) level, and diabetes-specific distress. Secondary outcomes are depression, anxiety, self-efficacy and adherence, and quality of life. Exposure data in terms of program uptake, use, time on each page, and program completion, as well as implementation feasibility will be conducted.

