### Sample Size and Retention

The sample of 210 enables detection of a small effect size of *f*
^
*2*
^=.046 in the multiple regressions. Although the study uses all allocated participants in the outcome analyses, efforts are made to maximize retention by maximizing rapport at the baseline assessment and collecting multiple means to contact participants, including email, landline, and mobile phone contact details, and by assertive follow-up. With these strategies, the study is aimed to have at least 70% retention at 12 months.

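### Covariates beyond the planned baseline measures are picked by observed imbalance between randomized arms, which costs precision and leaves the primary model open until the data are seen

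*Protocol article*

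**What the plan says.** The Statistical Analyses section opens with a covariate rule: "Preliminary analyses assess for baseline differences and subsequent analyses control for any observed differences". The primary regressions come in the next sentence, so they are among the later analyses that the rule governs. They are described as "predicting posttreatment and follow-up results from baseline measures and treatment contrasts", which puts some baseline measures in the model whatever the balance. The same section then plans mixed-model and repeated-measures ANOVAs and states no other covariate rule for them.

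Under Procedure, the article says "Computer-generated randomization occurs automatically". The abstract describes a "main RCT, which compares 3 treatments", and Recruitment and Sample states "The trial aims to enroll at least 210 participants". The rule names no test, threshold or prognostic criterion.

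**The concern.** In a properly randomized trial a baseline difference between arms is a chance event. A covariate is worth adjusting for because it predicts outcome, and imbalance carries no information about that. A rule driven by imbalance therefore goes wrong in two ways: it admits unbalanced variables that may be unrelated to outcome, and it gives no ground for including a strong predictor that happens to look balanced.

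Two things are at stake. One is precision that a fixed prognostic covariate would give at almost no cost. The other is transparency. Because the rule acts only once baseline data are in hand, and what counts as a difference is open, two analysts could follow it honestly and report different primary models. The trial has several primary outcomes and three follow-up times, so that freedom recurs. The covariate set also affects the planned multiple imputation, since an imputation model should contain the covariates of the analysis model.

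**Working it through.** **1. The plan's own figure.** Under Sample Size and Retention: "The sample of 210 enables detection of a small effect size of" f² = .046. Alpha, power and the number of tested predictors are not given there. With noncentrality λ = f² × N = .046 × 210 = 9.66 in the noncentral F test:

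- 2 tested df (three arms), alpha .05: power 79.5%; 80% needs N = 213.
- 1 tested df, alpha .025: 80% needs N = 210.
- 1 tested df, alpha .05: power 87%; 80% needs N = 173.

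The stated figure is reproduced under either of the first two settings.

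**2. What extra covariates cost in degrees of freedom.** With 2 tested df and k predictors in total, the denominator df are 210 − k − 1. Power is 79.50% with k = 2 (207 df) and 79.47% with k = 12 (197 df). The cost is negligible.

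**3. How often chance would trigger the rule.** Assume that assessing differences means independent tests at P<.05 on m variables. The chance of at least one difference under perfect randomization is 1 − 0.95^m:

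| m (assumed) | Chance |
|---|---|
| 5 | 23% |
| 10 | 40% |
| 15 | 54% |
| 20 | 64% |

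Any single prognostic variable enters the model in only about 5% of trials, however strong it is.

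**4. Simulation of the rule.** Assumed, not in the article: 70 per arm (210/3, ratio not stated), baseline-outcome correlation 0.6, ten independent candidate covariates of which one is prognostic with partial correlation r given the baseline outcome, entry at P<.05, and arm means 0, 0.2 and 0.4 SD for power. The baseline outcome is always in the model. There were 8,000 null and 5,000 alternative trials per setting.

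| r | Type I error, rule | Type I error, prespecified | Power, rule | Power, prespecified |
|---|---|---|---|---|
| 0.3 | 4.3% | 4.6% | 75.2% | 78.7% |
| 0.5 | 4.5% | 5.0% | 75.7% | 86.5% |
| 0.7 | 3.6% | 5.1% | 76.3% | 95.9% |

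The Monte Carlo standard error is √(.05 × .95/8000) = 0.24 points for type I error and √(.76 × .24/5000) = 0.6 points for power near 76%. A separate run of the same layout gave type I error of 3.7–4.2% under the rule, and power of about 76–77% against 79%, 87% and 97%.

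**5. Analytic check of the power gain.** The residual variance after the baseline outcome is 1 − 0.6² = 0.64, and the further covariate multiplies it by 1 − r². The between-arm sum of squares is 70 × (0.2² + 0 + 0.2²) = 5.6.

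- No further covariate: λ = 5.6/0.64 = 8.75, power 75.2%.
- r = 0.3: λ = 5.6/(0.64 × 0.91) = 9.62, power 79.3%.
- r = 0.5: λ = 5.6/(0.64 × 0.75) = 11.67, power 86.9%.
- r = 0.7: λ = 5.6/(0.64 × 0.51) = 17.16, power 96.6%.

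This agrees with the simulations. Under the rule, power stays close to that of a model with no further covariate.

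**The case against.** The next sentence of the article already puts baseline measures in the primary regressions. A reader might infer that the whole primary model rests on chance imbalance instead of prognosis. The text does not support that: the baseline value of the outcome, usually the strongest predictor, is presumably always included. The term is plural and undefined. If it covers several measures, baseline HbA1c and baseline distress may already be in every model, and that part of the gain is already secured. An imbalance in a variable already included would also change nothing.

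A reader might also infer inflated false positives, because the nominal P values ignore the selection step. The simulations show the opposite: the rule is slightly conservative.

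Nor does the article say that significance tests will be used. It speaks only of assessing differences. The statement that chance alters the model in more than half of trials needs 15 or more independent tests at 5%. With 5 to 10 variables the figure is 23–40%, and the psychological and self-care measures are plausibly correlated, which would lower it.

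Finally, an article commonly leaves the covariate list and the threshold to a fuller document, so their absence is no fault. That does not answer the point, because the article states the rule itself: a fuller plan must either follow it or depart from it.

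**Conclusion.** The point holds for the covariates added beyond the planned baseline measures. Choosing them by observed imbalance is a poor rule, stated explicitly, and it reaches the primary regressions and the later analyses.

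The consequence is modest: lost precision and a primary model open to analyst choice. Type I error is not inflated. The power forgone is about 3 to 4 points if one further covariate has a partial correlation of 0.3, and about 10 or 20 points at 0.5 or 0.7. The larger values require a strong additional predictor that the article does not identify. All these sizes rest on the assumptions listed in the working, above all equal allocation, a 5% entry test and the partial correlations. The fault in the rule itself rests on none of them, only on allocation being random. This is a cheap improvement to make and does not invalidate the trial.

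**What to change.** Delete the sentence. In its place, fix the covariates in advance for all models: the baseline value of the outcome, plus a short named list of prognostic variables chosen from those the trial collects at baseline. Baseline HbA1c and baseline diabetes-specific distress are examples; others belong on the list only if they are recorded, which cannot be checked because the measures table is not shown. State at the same time which baseline measures the regressions contain. Describe baseline balance without tests. Report any adjustment prompted by imbalance only as a labelled sensitivity analysis.

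The change takes a sentence or two, needs no change in sample size, and costs almost nothing in degrees of freedom. The small downside is that a chance imbalance in a variable not on the list is handled only in the sensitivity analysis.

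### The planned change-score repeated measures ANOVA duplicates the primary question with fewer participants and less precision; take its contrasts from an all-visits mixed model instead

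*Protocol article*

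**What the plan says.** The Statistical Analyses section of the protocol article names three analyses of the outcomes, in this order.

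1. The primary one: "The primary analyses will comprise multiple regressions, predicting posttreatment and follow-up results from baseline measures and treatment contrasts with multiple imputation" for missing data.
2. A check without imputation: "Mixed-model ANOVAs with repeated measures will also be applied to confirm whether effects are still obtained without imputations". The next sentence reads "Both methods allow an intention-to-treat approach to the data", and by its position it refers to these first two methods.
3. A further analysis, named after that sentence: "Repeated measures ANOVAs will be used to evaluate differences in change scores between the study time points among the 3 study conditions". The article does not say how this one handles missing visits.

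The Sample Size and Retention section adds "Although the study uses all allocated participants in the outcome analyses" and, on follow-up, "the study is aimed to have at least 70% retention at 12 months". It gives a detectable effect of f² = .046 with 210 participants, for the multiple regressions. Measures are taken at baseline and at 3, 6 and 12 months in three arms.

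**The concern.** The third analysis addresses the same between-arm question as the first two, but with a weaker tool. A standard repeated measures ANOVA works on complete rows: anyone missing a visit that it includes is left out. That does not fit the statement that all allocated participants are used in the outcome analyses. A change from baseline is also a less efficient way to use the baseline value than adjusting for it, which the primary regression already does.

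What is at stake is interpretation. Suppose the change-score ANOVA disagrees with the primary regression. The cause could simply be lost participants or lost precision, and readers would have no way to tell this from a fragile treatment effect. Suppose instead that the analyses agree. Readers may then take more comfort about dropout than the methods can give.

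**Working it through.** **Inputs from the article.** N = 210; f² = .046; retention at 12 months at least 70%; three arms, hence two treatment contrasts; four visits.

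**Assumptions (not in the article).** Two-sided alpha 0.05; 80% target power; two contrasts tested jointly; three predictors in the regression; correlation rho between baseline and follow-up; equal variance over time; equal allocation.

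**Step 1: the article's own figure.** Noncentral F test with lambda = f² × N and error df = N − k − 1.
- lambda = 0.046 × 210 = 9.66, with df 2 and 210 − 3 − 1 = 206. Power is 79.5%, and the f² detectable with 80% power is 0.0466. The stated .046 is reproduced.
- The result depends on the number of contrasts tested: power is 87.2% with one and 73.6% with three.

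**Step 2: participants lost.** 0.70 × 210 = 147, so up to 210 − 147 = 63 people are left out of any complete-row analysis that includes month 12, and more if others miss an intermediate visit. As a yardstick, the Step 1 F test at N = 147 has 63.0% power at f² = .046, and the detectable f² rises to 0.0669.

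**Step 3: precision lost.** With outcome variance σ² at each visit:
- change from baseline: 2σ²(1 − rho)
- baseline-adjusted regression: σ²(1 − rho²)
- ratio: 2(1 − rho)/(1 − rho²) = 2/(1 + rho)

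To carry this into power, f² is divided by the ratio:

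| rho | variance ratio | power, N = 210 | power, N = 147 |
|---|---|---|---|
| 0.5 | 2/1.5 = 1.33 | 66.5% | 50.1% |
| 0.7 | 2/1.7 = 1.18 | 72.3% | 55.5% |
| 0.9 | 2/1.9 = 1.05 | 77.3% | 60.6% |

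The size depends on rho. The direction does not, for any rho below 1.

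**Step 4: bias under dropout.** Simulation with two arms of 70, four visits, rho 0.6, true effect 0.40 SD and 1,500 runs; about 70% to 76% retained; Monte Carlo standard error about 0.004. In the second and third rows, dropout depends on the outcome in one arm only.

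| Dropout | Completers, change score | Completers, baseline-adjusted | Likelihood, all visits |
|---|---|---|---|
| Completely at random | 0.397 | 0.400 | 0.400 |
| At random (depends on previous value) | 0.354 | 0.434 | 0.397 |
| Not at random (depends on current value) | 0.424 | 0.483 | 0.468 |

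In the second row the two completer analyses miss the true value in opposite directions, while the all-visits likelihood model recovers it. In the third row the likelihood model is biased as well. Standard multiple imputation rests on the same missing-at-random assumption, so agreement between the two would not reveal this kind of dropout.

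**The case against.** The strongest reply is that the article's named check is the mixed-model ANOVA, not the change-score ANOVA. A reader might infer that none of the non-imputed analyses is intention-to-treat and that the sentence about both methods is wrong. The documents do not support this. That sentence comes before the change-score ANOVA and does not cover it. A mixed model fitted by likelihood on all available visits is consistent with it, and the article's statement about using all allocated participants favours that reading. Such estimation details are commonly left to a fuller document.

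A reader might also infer that the plan offers the non-imputed analysis as a test of the imputation assumption. It does not; it speaks only of confirming that effects are still obtained. Nor is the absence of a sensitivity analysis for informative dropout an error in an article of this kind. Regular therapist calls in one arm suggest that dropout rates may differ by arm, but dropout that depends only on arm is still missing at random in a model that includes arm.

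Three limits on size also stand.
- A change between two visits needs only those two visits, so it is too strong to say that anyone with any missed visit is dropped. The article does not state complete-case handling either.
- The 147 applies only to analyses that include month 12. The superiority hypothesis is set at 3 months, for which no retention figure is given.
- The power figures are for a regression F test and serve as a yardstick; they are not a power calculation for a repeated measures ANOVA.

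What remains is that the article commits to a third, weaker analysis whose standard form does not fit its own statement on who is analysed.

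**Conclusion.** The point holds for the change-score ANOVA. In its standard form it uses at most about 147 of 210 participants in any analysis with month 12 at the retention floor. For change from baseline, its variance is 1.18 to 1.33 times that of the baseline-adjusted regression at rho 0.7 to 0.5. It can also be biased under missing-at-random dropout where an all-visits likelihood model is not. These sizes rest on complete-row handling, an assumed rho and equal variances over time; the power figures also assume alpha 0.05 and two tested contrasts.

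The designated primary analysis, an imputed and baseline-adjusted regression, is not affected. This is a worthwhile improvement to a supporting analysis, not a threat to the trial's main result.

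**What to change.** State that the mixed-model ANOVA is a linear mixed model fitted by likelihood to all observed follow-up visits, with baseline as covariate, arm-by-visit terms and an unstructured covariance. Take the between-arm contrasts at 3, 6 and 12 months from it, and drop the change-score ANOVA. Nothing is lost: with baseline as covariate, an arm contrast at a visit is also the adjusted difference in change from baseline, and differences in change between follow-up visits are contrasts of the arm-by-visit terms. With this specification, participants with no follow-up visit add nothing to the contrasts; the imputed primary regression remains the analysis that includes everyone allocated.

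Add one sentence saying that agreement between the mixed model and the imputed regression is not evidence about informative dropout, since both assume missing at random. An optional, cheap addition is to rerun the planned imputation with imputed values made worse by 0.1 to 0.5 SD, separately by arm, and report where the conclusion changes.

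The cost is a few lines of plan and code, with no new data. The optional rerun adds a little analysis work.
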